# Comparison of four skin preparation strategies to prevent catheter-related infection in intensive care unit (CLEAN trial): a study protocol for a randomized controlled trial

**DOI:** 10.1186/1745-6215-14-114

**Published:** 2013-04-27

**Keywords:** Central venous catheter, Arterial catheter, Colonization, Bacteremia, Severely ill patient

## Abstract

**Background:**

Catheter-related infection is the third cause of infections in intensive care units (ICU), increasing the length of stay in ICU and hospital, mortality, and costs. Skin antisepsis is one of the most prevalent preventive measures. In this respect, it would appear preferable to recommend the use of alcoholic povidone iodine or chlorhexidine rather than aqueous povidone iodine. However, the data comparing chlorhexidine to povidone-iodine, both of them in alcoholic solutions, remain limited. Moreover, the benefits of enhanced cleaning prior to disinfection of skin that is not visibly soiled have yet to be confirmed in a randomized study.

**Methods:**

A prospective multicenter, 2×2 factorial, randomized-controlled, assessor-blind trial will be conducted in 11 intensive care units in six French hospitals. All adult patients aged over 18 years requiring the insertion of at least one peripheral arterial catheter and/or a non-tunneled central venous catheter and/or a hemodialysis catheter and/or an arterial pulmonary catheter will be randomly assigned to have all their catheters cared with one of four skin preparation strategies (2% chlorhexidine/70% isopropyl alcohol or 5% povidone iodine/69% ethanol with or without prior skin scrubbing). At catheter removal, catheter tips will be quantitatively cultured. Sets of aerobic and anaerobic blood cultures will be routinely obtained when a patient has fever, hypothermia, or other indications. In case of suspected catheter-related infection the patient’s form will be reviewed by an independent adjudication committee. We plan to enroll 2,400 patients (4,800 catheters). The main objective is to demonstrate that use of 2% alcoholic chlorhexidine compared to 5% alcoholic povidone iodine in skin preparation lowers the rate of catheter-related infection. The second endpoint is to demonstrate that enhanced skin cleaning prior to disinfection of skin that is not visibly soiled does not reduce catheter colonization. Other outcomes include comparison of skin colonization at catheter insertion site, comparison of catheter colonization and catheter-related bacteremia taking place during implementation of the four strategies of skin preparation, and cutaneous tolerance, length of hospitalization, mortality, and costs.

**Discussion:**

This study will help to update recommendations on the choice of an antiseptic agent to use in skin preparation prior to insertion of a vascular catheter and, by extension, of an epidural catheter and it will likewise help to update recommendations on the usefulness of skin scrubbing prior to disinfection when the skin is not visibly soiled.

**Trial registration:**

Clinicaltrials.gov number NCT01629550

## Background

Catheter-related infections represent the third cause of infections in intensive care units (ICUs) after pneumonia and complicated intra-abdominal infections [1]. These infections increase the length of ICU and hospital stay, mortality, and costs. Additional costs as high as $30,000 per survivor have been reported, including 1 extra week in the ICU and 2 to 3 additional weeks in the hospital [2]. Attributable mortality rates range from 0 to 35%, depending on the degree of control for severity of illness [2].

The physiopathology of catheter infection is now more clearly understood [2]. For short-term catheters such as those inserted in ICUs, catheter tip colonization arises during catheter insertion or, less frequently, by migration of skin organisms from the insertion site into the cutaneous catheter tract during catheter maintenance. The density of micro-organisms at catheter insertion site is therefore a major risk factor for short-term catheter-related infection, while skin antisepsis is one of the most effective preventive measures.

Povidone iodine and chlorhexidine are the two most commonly used antiseptic agents, both of them being available as aqueous and alcoholic formulations. Their respective efficacy in preventing catheter colonization and bloodstream infections has been compared in numerous studies. One meta-analysis including eight randomized trials and 4,143 short-term catheters, published in 2002, found that chlorhexidine solutions either in aqueous or alcoholic formulations significantly reduced catheter-related bloodstream infections by approximately 50% (RR, 0.51 (95% CI, 0.27-0.97)) compared to 10% for aqueous povidone iodine [3]. These findings were subsequently confirmed in other trials [4-6], leading in many countries, the USA [7], England [8], and France [9], to cessation of the recommendation of aqueous povidone iodine in catheter care. The superiority of chlorhexidine has been linked by some authors to a synergistic effect with alcohol, which has also been demonstrated with povidone iodine. Compared to aqueous 10% povidone-iodine, a double application of 5% povidone iodine in 69% ethanol reduced the incidence of catheter colonization (RR, 0.38 (95% CI, 0.22-0.65)) and catheter-related infection (RR, 0.34 (95% CI, 0.13-0.91)) in a randomized unit-crossover study that included 223 central venous catheters [10]. No significant effect was observed on bloodstream infections, but the study was underpowered to explore this issue.

Two French trials have directly compared alcoholic formulations of chlorhexidine and povidone iodine. The first one included 481 evaluable central venous catheters inserted into jugular or subclavian veins [11]. Use of a combination of 0.25% chlorhexidine gluconate, 0.025% benzalkonium chloride, and 4% benzylic alcohol was associated with a reduction by half in the incidence of catheter colonization (11.6% *vs.* 22.2% *P*= 0.002; incidence density, 9.7 *vs*. 18.3 per 1,000 catheter-days). A trend toward lower rates of catheter-related bloodstream infection was likewise noted (1.7% *vs.* 4.2% *P*= 0.09; incidence density, 1.4 *vs.* 3.4 per 1,000 catheter-days), notwithstanding the fact that the study was not powered to adequately explore this issue. However, lack of skin scrubbing (which is strongly recommended in France) prior to antiseptic administration, completion of the study in a single unit, and use of a combination of three compounds in the chlorhexidine arm all constituted obstacles to generalization of these findings. The second trial was a single-center before-after study comparing the efficacy of the same antiseptics as in the previous trial and included 435 central venous catheters in the povidone iodine arm and 371 central venous catheters in the chlorhexidine arm [12]. The switch from alcoholic povidone iodine to the chlorhexidine-based antiseptic solution was associated with a reduction in catheter colonization (11.2 *vs.* 15.5 per 1,000 catheter days, *P*=0.041) and a pronounced decline in catheter-related bacteremia (1.4 *vs.* 3.0 per 1,000 catheter days, *P*=0.052). Moreover, use of alcoholic povidone iodine was independently associated with an increased risk of catheter colonization or infection in multivariate cox model analysis (1.48, 95% CI, 1.01-2.15, *P*=0.043). This study nonetheless has several limitations, including its design, but it succeeds in confirming the superiority of chlorhexidine-based solutions over povidone iodine, even in alcoholic formulations, in care of central venous catheters.

The superiority of chlorhexidine over povidone iodine has been linked to quick bactericidal activity, poor inactivation by blood and other protein-rich biomaterials present on skin, and long-term antimicrobial suppressive activity. These findings have led the Centers for Disease Control and Prevention (CDC) to include in their 2011 recommendations [7] the use of alcoholic chlorhexidine at a concentration >0.5% as a first-line antiseptic in catheter care. However, they pointed out that data comparing chlorhexidine and povidone-iodine in alcoholic solutions are limited and recommended the organization of a large-scale study comparing alcoholic formulations of chlorhexidine and povidone iodine.

In addition, skin scrubbing reduces bacterial load and the amount of protein-rich biomaterials present on skin and may thereby enhance the efficacy of antiseptics. However, the benefits of enhanced skin cleaning prior to disinfection of skin that is not visibly soiled have never been confirmed in a randomized study. Its use, recommended in only a few countries such as France, is based on the results of a study showing a link between the amount of skin colonization before antiseptic application and catheter colonization [13]. These findings offer only indirect evidence in favor of skin scrubbing before skin antisepsis. The French Society of Hospital Hygiene (SF2H) recommends the systematic skin scrubbing prior to antisepsis while the CDC, on the other hand, indicates that antiseptics could be directly applied on clean skin [7].

The objectives of this study are to demonstrate in adult ICU patients (1) the ability of 2% chlorhexidine/70% isopropyl alcohol to decrease the rate of catheter-related infection compared with the use of 5% povidone iodine/69% ethanol and (2) the inability of skin scrubbing prior to disinfection to reduce catheter colonization when the skin is not visibly soiled.

## Methods

### Ethics statement

The study was approved by the local ethics committee (CPP Ouest III, France) on 21 May 2012 (Protocol# 12.02.06). Each patient will have oral and written information concerning the study design and outcomes. If the information cannot be delivered to the patient, it will be delivered to his/her relatives.

### Study design

The CLEAN study is a prospective multicenter, 2×2 factorial, randomized-controlled, assessor-blind trial involving 11 intensive care units in five French University-affiliated hospitals and one French general hospital and is designed to compare two antiseptics (2% chlorhexidine/70% isopropyl alcohol and 5% povidone iodine/69% ethanol) with or without prior skin scrubbing. Due to the different colors of the two solutions, nurses and physicians will not be blinded to the antiseptic agent used. However, the microbiologists assigned to process all of the cultures and the adjudication committee tasked with reviewing the outcomes other than colonization will be unaware of the patients’ arms.

Inclusions opened at the end of October 2012 and will close approximately 14 months later.

### Patients

All consecutive adult patients aged over 18 years, hospitalized in one of participating ICUs for an expected length of stay of >2 days and requiring insertion of at least one peripheral arterial catheter and/or a non-tunneled central venous catheter and/or a hemodialysis catheter and/or an arterial pulmonary catheter will be included in the trial. Exclusion criteria will be catheters inserted outside the ICUs, patients with a history of allergy to any of the antiseptic agents studied, patients likely to die within 48 h after admission, and use of catheters coated with antimicrobial agents.

### Randomization

Patients will be randomly assigned in a 1:1:1:1 ratio to have all their catheters cared with either 2% chlorhexidine/70% isopropyl alcohol (Chloraprep™, CareFusion™, Voisins le Bretonneux, France) or 5% povidone iodine/69% ethanol (alcohol Bétadine™, MEDA™ Pharma SAS, Paris, France) with or without prior scrubbing with an antiseptic scrub. Randomization will be stratified by hospital with the use of a web-based random-number generator producing permuted blocks to address for potential interhospital heterogeneity.

### Skin antisepsis

Antiseptic agents used will be:

– 5% povidone iodine/69% ethanol preceded or not by scrubbing insertion site with a detergent (4% povidone iodine, Betadine™ Scrub, MEDA™ Pharma).

– 2% chlorhexidine/70% isopropyl alcohol (applicator sponge soaked with the antiseptic, Chloraprep™) preceded or not by scrubbing insertion site with a detergent (4% chlorhexidine, Hibiscrub™, Molnlycke Health Care, Wasquehal, France).

According to the randomization arm, antiseptic strategy during catheter insertion and maintenance will be:

– One-step procedure. The physician who will insert the catheter will disinfect the skin using maximal barrier precautions (surgical hand antisepsis and wearing a gown, cap, mask, and sterile gloves). Antiseptic will be applied moving back and forth (2% chlorhexidine/70% isopropyl alcohol) or by circular movements (5% povidone iodine/69% ethanol) for 30 s, starting at the catheter insertion site and then expanding to the entire work area. Large sterile drapes will be applied once the work area dries. Catheters will then be inserted without any further application of antiseptic.

– Four-step procedure. The work area will be scrubbed by a nurse using sterile gauze soaked with detergent applied by circular movements for 15 s, rinsed with sterile water, and dried with sterile gauze. Antiseptic and large sterile drapes will then be applied by the physician using maximal barrier precautions as described in the one-step procedure. Finally, catheters will be inserted without any further application of antiseptic.

In order to avoid any risk of confusion, antiseptic kits containing all the products needed according to randomization arm will be available in the patient’s room; similarly, a poster showing how to carry out skin preparation will be displayed in the patient's room. Training for healthcare providers designed to homogenize skin preparation practices between units will be held before starting inclusions. A clinical research associate will be available at each participating Hospital to help with data collection and to monitor for adequate practices.

### Catheter insertion and maintenance

All study centers are to follow French recommendations (similar to those of the CDC) for catheter insertion and care. Use of the subclavian vein (except for hemodialysis catheter) and radial artery will be encouraged whenever possible. Catheters will be placed percutaneously using the Seldinger technique. Ultrasound guidance shall be used at the discretion of the attending physician. Before catheter insertion, the skin will be disinfected with the randomized antiseptic procedure assignment. After insertion, catheters will be dressed with semi-permeable non-chlorhexidine transparent dressing. For each unit, the same catheter and dressing types will be used for the duration of the study period. Catheter insertion sites will be inspected every day for signs of infection. Dressing will be changed every 72 h to 7 days according to center protocol or earlier if leaking, soiled, or wet (except for the first dressing changed 24 h after catheter insertion). Manipulation of lines and three-way stopcocks will be carried out with gauze moistened with 5% povidone iodine/69% ethanol in povidone iodine arms and 0.5% chlorhexidine/67% alcohol (Hibitane Champ™, Molnlycke Health Care, Wasquehal, France) in the chlorhexidine arm.

Use of antiseptic-containing dressings, topical antimicrobial ointments, antimicrobial filters, and line locks will not be allowed. Blood sampling through the central venous line will not be permitted. The decision to remove the catheter will be made solely by the patient’s physician, but ablation of the catheter when it is losing its usefulness will be encouraged. Patients leaving the ICU with their central venous catheter will undergo one peripheral and one central line blood culture and will be followed for 3 days after ICU discharge to monitor possible infectious complications. Any catheter infection occurring >3 days after ICU discharge will not be taken into account due to the risk of protocol violation during catheter manipulation or of maintenance by untrained healthcare providers.

### Cultures

Catheters will be removed aseptically and their distal 5cm will be sectioned with sterile scissors and placed in a sterile tube before being carried to the microbiology laboratory. Catheters will be cultured quantitatively by using a simplified technique of quantitative broth dilution culture [1,14].

Sets of aerobic and anaerobic blood cultures will be routinely obtained when a patient has fever, hypothermia, or other indications such as chills or sudden shock.

Skin colonization will be evaluated before catheter removal by using semi-quantitative insertion-site cultures. The insertion site will be sampled by pressing on the skin for 10 s a sterilized nutritive trypticase-soy agar plate containing antiseptic neutralizing agents (Count-tact™, 3P Pack+, Biomerieux™, Crapone, France).The plate will then be sent to the local microbiology laboratory and cultured for 48 h. The number of colony-forming units will be counted and classified as: sterile; 1 to 9 CFU; 10 to 49 CFU, 50 to 99 CFU, or ≥100 CFU per agar plate as previously done [9,15].

All cultures will be processed by the clinical microbiology laboratory according to standard methods without awareness of the randomization arm.

In cases of suspected catheter-related infection (that is, all the catheters removed with systemic inflammatory response syndrome (SIRS) or local signs of infection (pain or purulence) or positive catheter tip culture, or positive blood culture sampled 48 h before until 48 h after the catheter removal), the patient’s form will be reviewed by an independent adjudication committee. In the event of doubt, a complete blind patient record will be prepared by the clinical research associates. Two independent experts blinded to the randomization arm will classify these episodes according to infection definitions (see below). In case of disagreement, the opinion of a third expert will be sought.

### Data collection

– For each center: number of hospital beds, type of ICU (medical, surgical or mixed, number of ICU beds, number of admissions a year in ICU, mean Simplified Acute Physiology Score II (SAPS II) [16], mean length of stay in ICU, and details of procedures for catheter insertion and maintenance.

– For each patient included: demographic data (age, sex, weight, and height), SAPS II and Sequential Organ Failure Assessment (SOFA) [1] scores at admission, length of mechanical ventilation, use of catecholamines, clinical and microbiological data needed to confirm the diagnostic of catheter-related infection.

– For each catheter: catheter insertion date, insertion site, catheter removal date, use of ultrasound guidance, insertion using guidewire exchange, experience of the operator, IGS II and SOFA scores at catheter insertion, antibiotics at catheter insertion, antibiotics used during catheter stay, administration of parenteral nutrition, propofol or blood product administration, reason(s) for catheter withdrawal, catheter tip culture result, blood culture result, local signs at catheter insertion site, status of dressing at catheter removal, evolution of signs of infection at catheter withdrawal, number and results of blood cultures drawn within 48 h around catheter removal during catheter stay, and skin colonization at removal of catheter assessed using semi-quantitative insertion site culture.

Three audits will be conducted in each center, each of them including four catheter insertions and 10 dressing changes, the first one during the first 2 months of study, the second one after inclusion of 100 patients, and the last one after inclusion of 200 patients. The costs of each antiseptic strategy will be evaluated based on material and time needed for skin preparation.

### Definitions

French [9] and American [7] guidelines will be used by the blind adjudication committee.

– Catheter colonization will be defined as a quantitative culture tip showing at least one micro-organism at a concentration of 1,000 colonies forming 1 unit per milliliter (cfu/mL) or more.

– Catheter-related sepsis without bacteremia will be defined according to the combination of (1) fever (body temperature ≥38.5°C) or hypothermia body temperature ≤36.5°C), (2) catheter colonization, (3) regression of fever or hypothermia within the 48 h following catheter removal and without any change of antimicrobial therapy, or presence of pus at catheter insertion site, and (4) no other source of infection identified.

– Catheter-related bloodstream infection will be defined as the combination of (1) fever (body temperature ≥38.5°C) or hypothermia body temperature ≤36.5°C), (2) one or more positive peripheral blood cultures drawn 48 h before or after catheter withdrawal, (3) isolation of the same organism (same species and same susceptibility pattern) from the colonized catheter, or from the catheter insertion site, or a blood-culture differential time-to-positivity of 2 h or more, and (4) no apparent source of bacteremia other than the catheter. In patients with positive coagulase negative staphylococci bacteremia, at least two positive cultures obtained from separate blood samples will be mandatory.

– Major catheter-related infections will be either catheter-related sepsis without bacteremia or catheter-related bloodstream infections.

– Non-cultured catheters or catheters growing under 1,000 cfu/mL will be classified as catheter-related sepsis or bloodstream infections in case of sepsis without or with bacteremia and no other detectable source.

– Non-cultured catheters will be classified as not colonized unless there was sepsis with no other detectable cause.

### Outcomes

The main endpoint will be to demonstrate that compared to 5% povidone iodine/69% ethanol, use of 2% chlorhexidine/70% isopropyl alcohol for skin preparation lowers the rate of major catheter-related infection. The second endpoint will be to demonstrate that skin scrubbing prior to antiseptic application does not reduce catheter colonization when the skin is not visibly soiled. Other outcomes include comparison of colonization at catheter insertion site, catheter colonization, and catheter-related bacteremia, as well as cutaneous tolerance, length of hospitalization, mortality, and costs between the four strategies of preparation of skin. In particular, a comparison between 2% chlorhexidine/70% isopropyl alcohol not preceded by scrubbing and 5% povidone iodine/69% ethanol preceded by scrubbing will be carried out.

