### Sample size calculation

Assuming 5% of catheter-related infection rate in the 5% povidone iodine/69% ethanol group (that is, incidence density of 4 per 1,000 catheters days) and the use of at least two catheters per patient on average, 453 patients in each treatment arm will be required to demonstrate a 50% reduction of major catheter-related infection with the use of 2% chlorhexidine/70% isopropyl alcohol, with a power of 80% and a two-sided alpha risk of 5%. We plan to enroll 2,400 patients (4,800 catheters) to take into account the interaction between antiseptic efficacy and skin scrubbing and a maximum patient loss of 6%.

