### Statistical analysis

The data will be analyzed blindly with regard to treatment arms. An intention-to-treat analysis is scheduled, and it will include all patients except those with no catheter inserted and those who will have withdrawn their consent to participate in the study. No interim analyses are planned. Demographic data will be described in number and percentage or median and interquartile range for quantitative and qualitative variables and compared with χ^2^ test or Mann–Whitney, as appropriate. Kaplan-Meir curves of the risks of major-CRI and CR-BSI and catheter colonization will be plotted for each treatment group. Proportional hazard assumption will be assessed by plotting Schoenfield’s residuals with time.

Analysis of antiseptic efficacy will be carried out using a marginal Cox model stratified by centers [18]. This model takes into account the censored nature of the data and also accounts for intra-cluster (intra-patient) dependence (more than one catheter per patient) using a robust sandwich covariance matrix. The interaction between scrubbing and antiseptic effect will be sought first by forcing the interaction term in the final model. In the absence of interaction, analysis of skin scrubbing and chlorhexidine effects will be performed independently. For secondary endpoints the analyses will not be controlled for multiple testing.

Comparisons of skin cultures between groups will be assessed through multiple factor ANOVA (Center, scrubbing, antiseptic).

Analyses will be done using SAS 9.x (SAS Institute, Cary, NC,USA) and R (R foundation, Vienna, Austria) softwares.

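### The second objective is to demonstrate that scrubbing does not reduce colonization, but the protocol states no margin, confidence-limit criterion or sample-size basis for that claim

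*Protocol article*

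**What the plan says.** The same aim appears three times. The abstract (Methods) wants "to demonstrate that enhanced skin cleaning prior to disinfection of skin that is not visibly soiled does not reduce catheter colonization". The end of the Background sets out to demonstrate "the inability of skin scrubbing prior to disinfection to reduce catheter colonization when the skin is not visibly soiled". The Outcomes section makes it the second endpoint: "to demonstrate that skin scrubbing prior to antiseptic application does not reduce catheter colonization", again for skin without visible soiling.

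The Sample size calculation concerns a different comparison and a different outcome: "453 patients in each treatment arm will be required to demonstrate a 50% reduction of major catheter-related infection" with chlorhexidine, from an assumed 5% rate, at 80% power and two-sided 5% alpha. The increase to 2,400 patients (4,800 catheters) is attributed to the antiseptic-by-scrubbing interaction and up to 6% patient loss. No colonization rate, margin or power is given for scrubbing.

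Under Statistical analysis, the model is introduced for the antiseptic: "Analysis of antiseptic efficacy will be carried out using a marginal Cox model stratified by centers". Scrubbing is covered by one sentence: "In the absence of interaction, analysis of skin scrubbing and chlorhexidine effects will be performed independently". No section uses non-inferiority or equivalence wording.

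**The concern.** A demonstration that something has no benefit needs a statement of how small a benefit counts as none, and a rule for showing that larger benefits are excluded. The protocol gives neither. If the conclusion were drawn from a non-significant comparison, imprecision would work in favour of the claim: the fewer the colonization events, the likelier a real reduction goes undetected.

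The abstract's Discussion says the trial will help to update recommendations on whether scrubbing is useful when skin is not visibly soiled. The Background says the French hygiene society recommends systematic scrubbing, and the Discussion says nurses perform it several million times a year. A no-benefit statement from this trial would carry weight, so it needs a basis that supports it.

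**Working it through.** **1. The plan's own figure.** Two proportions, 5% against 2.5%, pooled variance under the null, no continuity correction, two-sided alpha 5%, power 80%:

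n = [1.96 × √(2 × 0.0375 × 0.9625) + 0.8416 × √(0.05 × 0.95 + 0.025 × 0.975)]² / 0.025² = 906 catheters per group after rounding up.

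At two catheters per patient, 906 / 2 = 453 patients, exactly as stated. This calculation contains nothing about scrubbing or colonization.

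**2. Inputs for the scrubbing comparison.**
- From the protocol: 2,400 patients, 6% loss, two catheters per patient, 1:1:1:1 allocation. Evaluable catheters = 2,400 × 0.94 × 2 = 4,512, so 2,256 per scrubbing group.
- Assumed, because the protocol gives no design value: colonization per catheter of 10%, 11.6%, 15% or 22.2%. The values 11.6% and 22.2% are the two arms of the first French trial described in the Background. That trial studied jugular and subclavian central venous catheters, whereas this one also includes arterial catheters, so a lower rate is possible.
- Assumed: design effect (DE) of 1.0 to 1.2 for several catheters in one patient.

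**3. Chance that a two-sided 5% test misses a true hazard ratio (HR) of 0.80.** Unscrubbed events e0 = 2,256 × rate / DE; scrubbed events e1 = 0.80 × e0; SE(log HR) = √(1/e0 + 1/e1); power = Φ(0.2231/SE − 1.96).

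Example at 10%, DE 1.0: e0 = 225.6, e1 = 180.5, SE = 0.0999, 0.2231/0.0999 = 2.234, power = Φ(0.274) = 0.61, so 39% missed.

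**4. Power to exclude HR 1.25 (no scrubbing against scrubbing) if there is truly no difference.** SE = 2/√(4,512 × rate / DE); power = Φ(ln 1.25/SE − 1.96), with ln 1.25 = 0.2231. The margin is illustrative.

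Example at 10%, DE 1.0: 451.2 events, SE = 0.0942, power = Φ(0.41) = 0.66.

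| Colonization | HR 0.80 missed (DE 1.0 to 1.2) | Power to exclude HR 1.25 (DE 1.2 to 1.0) |
|---|---|---|
| 10% | 39% to 47% | 58% to 66% |
| 11.6% | 33% to 41% | 64% to 72% |
| 15% | 22% to 30% | 75% to 83% |
| 22.2% | 9% to 14% | 90% to 94% |

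**5. Cross-check on simple proportions.** Treating catheters as independent, a 20% relative reduction is missed with probability 35% at 10%, 28% at 11.6%, 16% at 15% and 4% at 22.2%. These figures are somewhat lower but show the same pattern.

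On the absolute scale, non-inferiority at 80% power and one-sided 2.5% alpha with a 10% rate needs 14,128 catheters per group for a 1-point margin, 3,532 for 2 points and 1,570 for 3 points, against 2,256 available. Whether the planned size is enough therefore turns on a margin that the protocol does not fix.

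**6. Direction of the effect of imprecision.** By the formula in step 3, at 10% colonization and DE 1.0, a true HR of 0.80 is missed 82% of the time with 500 catheters per group, 68% with 1,000 and 39% with 2,256.

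**The case against.** The strongest reply is that the flaw lies partly in what a reader might infer. It is tempting to say that the plan will treat p > 0.05 as proof that scrubbing does nothing. The protocol nowhere says so. It names the Cox model for antiseptic efficacy and does not spell out the test for scrubbing. A rule for reading the confidence interval could also sit in an analysis plan that is not shown. This stands as a limit on the wording: what the document supports is that no margin or criterion is stated. It does not dispose of the point, because a margin defines the objective and underlies the sample size, and both are printed here without one.

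Second, the risk depends heavily on the colonization rate. Quoting only the 10% row would overstate it, since at 22.2% few trials would miss a 20% reduction. That is right, and the full range is shown for that reason.

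Third, a reader might infer either that the trial is too small for this objective or that it can comfortably support a margin. Neither follows without a margin and a rate. At 10% colonization, power for HR 1.25 is only 58% to 66%; at 22.2% it is 90% to 94%.

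Finally, this is the second objective. The primary comparison and its sample size are untouched, and the protocol does not say that scrubbing would be dropped on a null result. All of that is accepted.

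**Conclusion.** The point holds in this form: the protocol sets out to demonstrate absence of benefit, and its printed design has no element that could establish it. A non-significant difference would not do so.

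If no better rule is supplied, a true HR of 0.80 would go undetected in roughly 9% to 47% of trials, depending on a colonization rate between 22.2% and 10% and a design effect of 1.0 to 1.2. The protocol gives no design value for either, so these figures are conditional and do not predict this trial's result. For a margin of HR 1.25, taken only as an illustration, the planned size gives about 80% power (75% to 83%) at 15% colonization and clearly more at 22.2%, but falls short at 10% and 11.6%.

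The documents do not support the stronger statement that the investigators will read a null p-value as proof.

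**What to change.** Make one of two changes before unblinding.

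(a) Reword the second objective in the abstract, Background and Outcomes as estimating the effect of scrubbing on catheter colonization with its 95% confidence interval, and drop the claim to demonstrate no reduction. This needs no margin and is sufficient by itself.

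(b) Keep a confirmatory aim, restated as non-inferiority of no scrubbing to scrubbing on colonization. The steering group justifies a margin. Success is claimed only if the upper 95% confidence limit of the hazard ratio (no scrubbing against scrubbing) lies below it. The sample size section then states the assumed colonization rate and the power at the planned size. The documents give no basis for a particular margin, so none is proposed here.

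Cost: protocol and analysis-plan wording and, for (b), agreement on a margin. No extra patients or data are needed. The downside is that the claim is softened under (a) and harder to win under (b), where a narrow margin or a low colonization rate may leave power that has to be reported as inadequate.
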